### Adverse Events and Assessment of Safety

After participants provided informed consent and enrolled in the study, any adverse events were collected and recorded until the end of the study period. Adverse events that occurred after consent was signed, but before receiving the study intervention was reported as not related to our intervention. Any serious adverse event that occurred would be reported to the principal investigator and documented.

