**Conclusions:**

This randomized controlled trial will provide evidence on the treatment effects and safety of TAAT versus ILCD among children with overweight or obesity with gastric-heat and dampness-obstruction syndrome, in reducing body weight and improving cardiometabolic risks. Exploratory aims include potential underlying mechanisms of the 2 kinds of interventions, based on biosamples.

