### Interventions

#### Experimental Group (TAAT Group)

Specialized TCM clinicians conducted TAAT following a standardized procedure. The location and operation of the ear acupoints followed the guidelines outlined in the “National Standard of the Peoples Republic of China for Nomenclature and Location of Auricular Points (GB/*t* 13734-2008).” In addition, all TCM clinicians had received specialized training to ensure a comprehensive understanding of the auricular acupressure intervention program and to standardize the procedures performed by different clinicians.

The study selected the following ear acupoints for acupressure treatment: Shenmen (TF4), Xiaoping (TG2), Endocrine (CO18), Stomach (CO4), Mouth (CO1), and Subcortex (AT4) (refer to Figures 1 and 2) [24]. The acupressure was administered using an opaque patch with Vaccaria seed. Participants were instructed to apply pressure for 1 minute before and after meals each day, for a total of 2 to 3 days per week. They were followed weekly and received a 3-course treatment, with 1 course per month.

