#### Control Group (ILCD Group)

Participants were required to limit their daily carbohydrate intake to 50 g or less, while their dietary calorie intake was not restricted for nonconsecutive 7 days of 2 weeks, corresponding to 14 days in a month. On the remaining days, participants should maintain their normal diet. The intervention period lasted for 1 month, followed by a 2-month follow-up period [20].

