### Follow-Up Period

First, a WeChat group was created for parents of participants to facilitate communication and monitoring about diet and exercise recording, as well as scheduling follow-up appointments. Second, adherence to the study interventions were uniformly assessed in both groups at each visit. Third, if participants missed any visits, investigators would contact them directly by telephone to encourage continued participation and evaluate barriers.

The research assistant attempted to establish contact with the missed participants. A dropout participant was defined as someone who had not been reached for 3 months. If participants decided to withdraw before completion, all collected data would be remained for analysis.

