**Assessments**														
	General investigation			N/A		✔		✔		✔		N/A		
	Anthropometry (Height, Weight, WC^b^, and BP^c^)			N/A		✔		✔		✔		N/A		
	Body fat content			N/A		✔		✔		✔		N/A		
	Indexes of liver and renal functions			N/A		✔		✔		✔		N/A		
	Indexes of glucose metabolism			N/A		✔		✔		✔		N/A		
	Levels of serum lipid			N/A		✔		✔		✔		N/A		
	TCM^d^ syndrome score			N/A		✔		✔		✔		N/A		
	Gut microbiota			N/A		✔		✔		N/A		N/A		
	Dietary data			N/A		✔		✔		✔		N/A		
	Exercise data			N/A		✔		✔		✔		N/A		
	Adverse events			N/A		N/A		✔		✔		N/A		

^a^N/A: not applicable.

^b^WC: waist circumference.

^c^BP: blood pressure.

^d^TCM: Traditional Chinese Medicine.

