### Randomization and Blinding

Participants were randomly assigned to either the experimental or control group through a simple randomization process generated by the R Language (version 4.2.2; R core team). This process was designed by the clinical trial unit of the Children’s Hospital of Fudan University and follows a 3:1 allocation ratio.

The study coordinator, who was not involved in data collection, performed the allocation. The randomization list was kept strictly confidential. Allocation was done by the study coordinator in a sequentially numbered fashion using identical, opaque, sealed envelopes. The recruiting clinicians were blinded to study group allocation and did not have access to the allocation sequence.

Eligible participants were enrolled by trained clinicians. The study coordinator independently assigned participants to either the intervention or control groups. Outcome observers were blinded. The analysis team received aggregated data obtained for the control and experimental groups. Study participants could be blinded, but they were scheduled for separate follow-up dates.

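### The adverse-event section does not tie the TAAT-versus-ILCD safety comparison to the 1- and 3-month assessments common to both arms, although weekly follow-up is stated for TAAT only

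*Protocol article*

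**What the plan says.** All references are to the protocol article.

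- **Adverse Events and Assessment of Safety:** after consent and enrolment, "any adverse events were collected and recorded until the end of the study period". The section gives a time window. It does not say how or at which contacts events are elicited, or which events enter the comparison.
- **Table 1 (Participant Timeline):** the row "Adverse events" is ticked at 1 month and at 3 months, with no distinction by arm. Auricular acupressure is ticked at both time points, the diet at 1 month only.
- **Experimental Group (TAAT Group):** "They were followed weekly and received a 3-course treatment, with 1 course per month".
- **Control Group (ILCD Group):** "The intervention period lasted for 1 month, followed by a 2-month follow-up period". No interim contact is mentioned, and the Abstract calls the diet self-administered.
- **Follow-Up Period:** for both arms, "a WeChat group was created for parents of participants to facilitate communication and monitoring about diet and exercise recording", and also to schedule appointments. Uniformity between arms is promised for adherence: "adherence to the study interventions were uniformly assessed in both groups at each visit". No such statement is made for adverse events.
- **Randomization and Blinding:** of the participants, "they were scheduled for separate follow-up dates".
- **Abstract, Conclusions:** the trial "will provide evidence on the treatment effects and safety of TAAT versus ILCD". The closing Conclusion repeats the comparative safety aim.

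**The concern.** How many mild events are recorded depends on how often someone is in a position to hear of them. The safety section accepts any event up to study end, and the only weekly schedule stated belongs to one arm. A report made in passing at a weekly TAAT contact would qualify for recording. An ILCD family has no stated equivalent between the 1- and 3-month visits apart from the WeChat group. A single count over three months would also set three months on TAAT against one month on ILCD plus two months off it.

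What is at stake is the comparative safety statement. TAAT could look less safe than ILCD, or ILCD safer than it is, because of contact and exposure and not because of the treatments. An analysis plan could restrict the comparison later only if the form shows where each report came from, and it cannot recover events that were never elicited.

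**Working it through.** The article gives no adverse-event rate, capture rate or safety test, so there is no stated figure to reproduce. The check sets the schedules side by side and then illustrates what unequal capture would do.

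**1. Stated contacts and exposure**

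| | TAAT | ILCD |
|---|---|---|
| Treatment (Interventions, Table 1) | 3 months | 1 month |
| Stated contacts, month 1 | weekly: 30/7 ≈ 4 | 1 (1-month visit) |
| Stated contacts, 3 months | weekly: 90/7 ≈ 12 to 13 | 2 (1- and 3-month visits) |
| Scheduled adverse-event assessments (Table 1) | 2 | 2 |

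The last row is equal and the rows above it are not. Nothing in the safety section says that the last row governs the comparison.

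**2. Coverage under an assumed recall window.** Suppose a mild event is reported only if a contact follows within L days. Weekly contact then covers all days for L ≥ 7. Visits at days 30 and 90 cover L/30 of month 1 and 2L/90 of the three months (L ≤ 30).

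| L (assumed) | Month 1 | 3 months |
|---|---|---|
| 7 | 7/30 = 23% | 14/90 = 16% |
| 14 | 14/30 = 47% | 28/90 = 31% |
| 21 | 21/30 = 70% | 42/90 = 47% |
| 30 | 30/30 = 100% | 60/90 = 67% |

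The result depends strongly on L. At 30 days there is no gap in month 1.

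**3. Effect on a comparison with no true difference.** Let the true risk p be equal in both arms, with capture c_T in TAAT and c_I in ILCD. The apparent risk ratio is p·c_T / (p·c_I) = c_T / c_I. With c_T = 0.9 and c_I = 0.9, 0.7, 0.5 or 0.3 (all assumed), it is 1.0, 1.29, 1.8 or 3.0.

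The chance of P<.05 in a two-sided two-proportion z test uses 150 and 50 children (Sample Size section). The article plans no such test; it serves only as a yardstick. Worked for p = 0.20, c_T = 0.9, c_I = 0.5:

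- Observed risks are 0.18 and 0.10. The pooled risk is (27 + 5)/200 = 0.16.
- Null SE = √(0.16 × 0.84 × (1/150 + 1/50)) = 0.0599.
- Alternative SE = √(0.18 × 0.82/150 + 0.10 × 0.90/50) = 0.0528.
- z = (0.08 − 1.96 × 0.0599)/0.0528 = −0.71, so the probability is about 0.24.

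| True risk (assumed) | 0.9 v 0.9 | 0.9 v 0.7 | 0.9 v 0.5 | 0.9 v 0.3 |
|---|---|---|---|---|
| 10% | 5% | 5% | 11% | 24% |
| 20% | 5% | 8% | 24% | 55% |
| 30% | 5% | 12% | 39% | 80% |

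**4. After the change.** If only events elicited by the same questions at the two common visits are compared, both arms have the same scheduled opportunities to report. The contact-schedule part of the distortion then largely disappears. At 1 month both arms are also on treatment, so the exposure difference is removed as well.

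**The case against.** The strongest reply is that the safety section sets a window and Table 1 sets the assessments. Read together, they can mean the same two enquiries for every child, each covering the time since consent. Several points support that reading:

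- The weekly sentence stands in the treatment description, and no section says that events are asked about or recorded at those contacts.
- The Objective and Trial Design section says that the TCM clinicians, who knew the allocation, took no part in the research that followed.
- The ILCD section does not exclude interim contact. Parents in both arms had the WeChat group and could have reported problems there, and missed visits prompted a telephone call.
- This is a condensed article. A full protocol (version 2.0) and a case report form exist and may settle how events are elicited.

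Most of this stands, and it limits the finding. A reader might infer that harms are in fact counted on different schedules, or that TAAT will be shown as less safe with some stated probability. The documents support neither. The first needs evidence that weekly contacts generate adverse-event records. The second rests on assumed recall, capture and event rates and on a test that the article does not plan. Nor do the documents describe any ILCD side effects that would be missed; the Discussion mentions side effects for TAAT only. A higher three-month count in TAAT could also reflect longer exposure.

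The objection does not remove the gap in the wording. Collection of any event to study end obliges staff to record what they hear, Table 1 puts no ceiling on that, and uniform assessment is promised for adherence alone. The point is therefore about what the article states, and not about detail left to another document.

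**Conclusion.** The point holds as a risk in the wording that should be closed. Open-ended collection, a weekly schedule stated for one arm, three months of treatment against one, and a comparative safety aim stand together without a rule on which events are compared. If weekly TAAT contacts yield records, the likely direction is relative over-counting in TAAT, which works against the experimental arm.

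The size cannot be given from the documents. Under the assumptions shown, the apparent risk ratio with no true difference runs from 1.0 to 3.0, and the chance of a nominally significant difference from 5% (no distortion) to 80% in the most extreme case. These figures show sensitivity and are not estimates. The primary outcome is not affected.

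**What to change.** - In Adverse Events and Assessment of Safety, state that the between-arm comparison uses events elicited with the same questions at the Table 1 visits common to both arms. Make the 1-month comparison the main one, because both arms are then on treatment.
- Add a source-of-report field to the case report form.
- Show events first reported at other contacts, and all events regardless of source, in separate descriptive tables by arm. Leave serious adverse event reporting as it is.
- If ILCD children are in fact also contacted weekly, say so in the Control Group section. That would settle the contact imbalance, though not the difference in treatment duration.

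**Cost.** One paragraph of wording and one form field, with no extra visits or patients. The comparative table will omit some mild TAAT events, which stay visible in the descriptive tables. For children already followed (112 enrolled by November 2024), the source of a report may not be recoverable, and this should be stated. A new symptom checklist for later enrolees only would create two ascertainment methods within the trial. It should be left out, or used descriptively.

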### Data Management and Monitoring

Trained clinicians were input data onto a paper-based clinical research form designed by the research team. Once data collection was complete for each participant, it would be entered into an electronic database with built-in checks to ensure completeness. Data monitoring has occurred periodically throughout the study. We used access to create a database, and 2 investigators independently performed dual data entry twice. Once verified, the database was saved appropriately. After confirming the accuracy of the database, it was locked and submitted to an independent statistical team for analysis.

### Statistical Analysis

Primary statistical analyses were conducted using the intention-to-treat strategy. Sensitivity analyses were performed using per-protocol set analysis.

#### Analysis of Primary Outcome

The primary outcome in this study was the change in body weight from baseline to 1 month. A generalized linear model (GLM) was used to compare the difference in weight change between the groups, with the baseline body weight as the covariate, to obtain the estimate of the mean difference in body weight change and its 95% CI, using Gaussian for family function and identity for link function.

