### Sample Size

The primary outcome was the change in body weight from baseline to 1 month. The sample size calculation was based on the difference in weight change between the 2 groups: the TAAT group and the ILCD group.

Our pilot data from 12 patients revealed a weight loss of 1.9 kg after 4 weeks of TAAT and a weight reduction of 1.4 kg after 4 weeks of ILCD, with an SD of 1.1 kg. We assumed a 0.5 kg difference in weight reduction between the 2 arms, power of 0.80, a 2-sided α of .05, and a sample size ratio of 3:1, a minimum sample size of 150 for the TAAT group and 50 for the ILCD group were required, respectively. Assuming a dropout rate of 15%, the trial enrolled at least 240 participants. The “test for 2 means module” of the PASS 16.0 software was used.

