#### Analysis of Secondary Outcomes

GLM was used to obtain differences in effect sizes and their 95% CI for continuous variables between groups. Categorical variables were described in absolute numbers (percentages) and GLM was used to obtain differences in effect values and their 95% CI, using logistic for family function and logit for link function.

Statistical analyses were conducted using Stata 16.0 software (StataCrop). All statistical tests were 2-sided with a significance level of α=.05. Differences were considered statistically significant at *P*<.05.

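### With 3:1 allocation, the primary GLM should specify a standard error that stays valid if weight change varies more in one arm than in the other

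*Protocol article*

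**What the plan says.** Under Analysis of Primary Outcome, the protocol article models the one-month change in weight "with the baseline body weight as the covariate" and "using Gaussian for family function and identity for link function", and reports the mean difference with its 95% CI. Under Analysis of Secondary Outcomes, the same class of model serves the other continuous measures: "GLM was used to obtain differences in effect sizes and their 95% CI for continuous variables between groups". That section also names Stata 16.0 and states the error rate: "All statistical tests were 2-sided with a significance level of α=.05". Neither section says how the standard error is to be obtained.

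Under Randomization and Blinding, the assignment process "follows a 3:1 allocation ratio". The Sample Size section sets 150 children for TAAT and 50 for ILCD, using one pilot figure for both arms, "with an SD of 1.1 kg". The pilot had 12 patients, and no SD is given by arm. The only sensitivity analysis named under Statistical Analysis is per-protocol, which changes who is analysed and leaves the variance assumption as it is.

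**The concern.** The trial asks whether mean weight change differs between arms. A Gaussian, identity-link GLM with the default standard error estimates one dispersion for everyone, so its test is calibrated for equal means together with equal residual variances.

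At 3:1 those two things come apart. About three quarters of the pooled variance comes from the 150 TAAT children. With equal variances, three quarters of the uncertainty in the difference comes from the 50 ILCD children (1/50 against 1/150). If the ILCD arm is the more variable, the pooled figure understates the uncertainty, so the interval is too narrow and the test rejects too often. If the TAAT arm is the more variable, the interval is too wide and power is lost. The primary P value and 95% CI are exposed, and so are those of the continuous secondary outcomes.

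**Working it through.** **Inputs from the protocol article.** Difference: "We assumed a 0.5 kg difference in weight reduction between the 2 arms". Error rates: "power of 0.80, a 2-sided α of .05". SD 1.1 kg; 150 TAAT and 50 ILCD; dropout 15%.

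**Input that is assumed.** r = ILCD SD / TAAT SD. The article does not give it, so a range is shown.

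**Step 1: the plan's own figure.** For the smaller arm, n = (1.960 + 0.842)² × 1.1² × (1 + 1/3) / 0.5² ≈ 50.7, so 51 ILCD and 153 TAAT. At 50/150, SE = 1.1 × √(1/150 + 1/50) = 0.180 and power is Φ(0.5/0.180 − 1.96) ≈ 0.795. The stated 150/50 is reproduced within rounding. The enrolment target of 240 also follows, since 204/0.85 = 240. The calculation takes r = 1.

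**Step 2: variance used against true variance.** In units of the TAAT variance:

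- Model-based: [(150 + 50r²)/200] × (1/150 + 1/50) = (3 + r²)/150
- True: 1/150 + r²/50 = (1 + 3r²)/150
- True over model-based: f = (1 + 3r²)/(3 + r²)

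With equal arm sizes the corresponding ratio is (1 + r²)/(1 + r²) = 1 for every r. The sensitivity therefore comes from the allocation ratio.

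**Step 3: type I error with equal means.** Two-sided error = 2 × [1 − Φ(1.96/√f)]. Half falls in each direction, and CI coverage is one minus the total.

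| r | f | Two-sided error | In favour of TAAT | 95% CI coverage |
|---|---|---|---|---|
| 0.67 | 0.680 | 1.7% | 0.9% | 98% |
| 1 | 1.000 | 5.0% | 2.5% | 95% |
| 1.25 | 1.247 | 7.9% | 4.0% | 92% |
| 1.5 | 1.476 | 10.7% | 5.3% | 89% |
| 2 | 1.857 | 15.0% | 7.5% | 85% |
| 3 | 2.333 | 20.0% | 10.0% | 80% |

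**Step 4: simulation.** The baseline-adjusted model was simulated at 150/50 with equal means, 30,000 runs per scenario.

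| r | Model-based SE, two-sided error | HC3 SE, two-sided error |
|---|---|---|
| 0.67 | 1.8% | 4.6% |
| 1 | 5.1% | 5.0% |
| 1.25 | 8.3% | 5.0% |
| 1.5 | 10.8% | 5.1% |
| 2 | 15.1% | 5.0% |

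At 180/60, the 240 enrolled with no loss, the model-based rates were 10.7% at r = 1.5 and 15.4% at r = 2.

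**Step 5: the opposite direction.** Assume TAAT SD 1.65 kg and ILCD SD 1.1 kg.

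- True variance: 2.7225/150 + 1.21/50 = 0.04235, so SE 0.206
- Model-based variance: [(150 × 2.7225 + 50 × 1.21)/200] × (1/150 + 1/50) = 0.0625, so SE 0.250
- Power for 0.5 kg, model-based: Φ[(0.5 − 1.96 × 0.250)/0.206] ≈ 52%
- Power for 0.5 kg, variance correctly estimated: Φ[(0.5 − 1.96 × 0.206)/0.206] ≈ 68%

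**Step 6: what the pilot can tell.** The article does not say how the 12 patients were split. If it was 6 and 6 (assumed) and the true SDs were equal, the observed SD ratio would lie between 0.37 and 2.67 in 95% of such pilots (square roots of the F(5,5) quantiles). So small a pilot says almost nothing about r in either direction.

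**The case against.** Three objections carry weight.

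**The article does not prescribe a pooled standard error.** It fixes the family, link, covariate and estimand. The same GLM can be fitted with robust standard errors without withdrawing a word, and an analysis plan that is not shown may already say so. This stands. It means the article cannot be said to contain an error here; the point concerns the model run at its default.

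**Unequal variance is not in evidence, and neither is its direction.** The article uses one SD for both arms. A reader might infer from the self-administered diet that ILCD results must be more variable. But TAAT children also apply the pressure themselves at home (Experimental Group section), and adherence is assessed in the same way in both arms (Follow-Up Period section). The difference in delivery establishes neither inequality nor direction. This stands too, though nothing in the article supports equality either.

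**The size is easily overstated.** A reader might infer that the test could declare TAAT superior at two to three times the stated 5%. The 10.7% and 15.0% at r = 1.5 and 2 count false rejections in both directions. False findings in favour of TAAT are 5.3% and 7.5%, which is two to three times the 2.5% per-direction rate but only about 1.1 to 1.5 times 5%. Reaching 10% in that direction needs an ILCD SD about three times the TAAT SD.

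It can also be said that baseline-adjusted Gaussian regression is standard and matches the single-SD sample size calculation. That is true, but the usual tolerance of unequal variances relies on similar arm sizes, which this trial gives up by design.

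**Conclusion.** The point holds as a conditional robustness improvement. At 150:50, the primary GLM with its default standard error is calibrated only if the arms have the same residual variance, and the article has no information that would settle this. The inflation and coverage figures in the tables rest on three assumptions: a model-based standard error, a given SD ratio, and ILCD as the more variable arm. With the ratio reversed, the cost is lost power. At r = 1 nothing is wrong. The documents do not support saying that the trial's error rate is in fact inflated. They do support choosing, in advance, a standard error for which the question does not arise.

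**What to change.** Keep the GLM, the baseline-weight covariate and the mean-difference estimand. Add one sentence to the primary analysis stating that the standard error, 95% CI and P value use a heteroscedasticity-consistent variance. In Stata, `regress change i.arm baseline_weight, vce(hc3)` gives the same point estimate as the Gaussian, identity-link GLM. A residual variance estimated separately by arm is an acceptable alternative. Apply the same rule to the continuous secondary outcomes, and report the SD of weight change by arm. If the analysis plan already specifies this, a cross-reference is enough.

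The cost is one command option and one sentence, with no new data or patients. If the variances are equal, simulated power for 0.5 kg falls from 78.9% to 78.3%, a loss of 0.6 percentage points. The choice should be fixed before anyone sees outcome data by arm, so that the standard error is not selected after the fact.
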